#### *c. Post Study Follow up and Procedures*

Unless there are any SAEs that need to be followed up closely, no post study follow-up and procedures need to be performed after the final study visit.

#### *d. Discontinuation Visit and Procedures*

Participants are free to withdraw from the study at any time without any consequence. Participants should be listed as having withdrawn consent only when they no longer wish to participate in the study and no longer authorise the study team to continue to obtain their outcome data.

Participants who withdraw from the study or are lost to follow-up after signing the ICF will not be replaced. The reason for participant withdrawal from the study will be recorded on the appropriate CRF.

## **7. TRIAL MATERIALS**

### **7.1. Trial Product (s)**

At the time of writing (02 Nov 2022), five COVID-19 vaccines (the monovalent mRNA vaccines BNT162b2 and mRNA-1273, the bivalent Comirnaty (Original/Omicron BA.4/5) and Moderna/Spikevax (Original/Omicron BA.1) vaccines, and the non-mRNA Nuvaxovid) have been authorised by HSA for use in Singapore. WHO approved Covaxin under the EUL procedure for use in two doses for primary vaccination. The booster is not approved in the EUL.

## **7.2. Storage and Drug Accountability**

At the time of writing (02 Nov 2022), five COVID-19 vaccines (the monovalent mRNA vaccines BNT162b2 and mRNA-1273, the bivalent Comirnaty (Original/Omicron BA.4/5) and Moderna/Spikevax (Original/Omicron BA.1) vaccines, and the non-mRNA Nuvaxovid) have been authorised by HSA for use in Singapore. The storage condition, dosing, formulation and administration of the vaccines used in this study will be according to prevailing recommendations provided by MOH and the conditions of the PSAR approval. This study is following the MOH's guideline of giving BNT162b2 at IM 30 mcg (0.3 mL) per dose, mRNA-1273 at IM 50 mcg (0.25 mL) per dose, non-mRNA Nuvaxovid at IM 5mcg (0.5mL) per dose, Comirnaty Bivalent (Original/Omicron BA.4/5) at IM 30 mcg (0.3 mL) per dose, and Moderna/Spikevax Bivalent (Original/Omicron BA.1) at IM 50 mcg (0.5 mL) per dose. The booster dose is meant as a single dose.

WHO approved Covaxin under the EUL procedure for use in two doses for primary vaccination. The storage condition, dosing, formulation and administration of the vaccines used in this study will be according to the package insert approved by WHO EUL. As Covaxin has not been approved for booster, this study will be investigating Covaxin as a booster dose at single IM 6ug (0.5ml) per dose.

## **8. TREATMENT**

### **8.1. Rationale for Selection of Dose**

At the time of writing (02 Nov 2022), five COVID-19 vaccines (the monovalent mRNA vaccines BNT162b2 and mRNA-1273, the bivalent Comirnaty (Original/Omicron BA.4/5) and Moderna/Spikevax (Original/Omicron BA.1) vaccines, and the non-mRNA Nuvaxovid) have been authorised by HSA for use in Singapore. The storage condition, dosing, formulation and administration of the vaccines used in this study will be according to prevailing recommendations provided by MOH and the conditions of the PSAR approval. This study is following the MOH's guideline of giving BNT162b2 at IM 30 mcg (0.3 mL) per dose, mRNA-1273 at IM 50 mcg (0.25 mL) per dose, non-mRNA Nuvaxovid at IM 5mcg (0.5mL) per dose, Comirnaty Bivalent (Original/Omicron BA.4/5) at IM 30 mcg (0.3 mL) per dose, and Moderna/Spikevax Bivalent (Original/Omicron BA.1) at IM 50 mcg (0.5 mL) per dose. The booster dose is meant as a single dose.

WHO approved Covaxin under the EUL procedure for use in two doses for primary vaccination. The storage condition, dosing, formulation and administration of the vaccines used in this study will be according to the package insert approved by WHO EUL. As Covaxin has not been approved for booster, this study will be investigating Covaxin as a booster dose at single IM 6ug (0.5ml) per dose.

### **8.2. Study Drug Formulations**

At the time of writing (02 Nov 2022), five COVID-19 vaccines (the monovalent mRNA vaccines BNT162b2 and mRNA-1273, the bivalent Comirnaty (Original/Omicron BA.4/5) and Moderna/Spikevax (Original/Omicron BA.1) vaccines, and the non-mRNA Nuvaxovid) have been authorised by HSA for use in Singapore. The storage condition, dosing, formulation and administration of the vaccines used in this study will be according to prevailing recommendations provided by MOH and the conditions of the PSAR approval. This study is

following the MOH's guideline of giving BNT162b2 at IM 30 mcg (0.3 mL) per dose, mRNA-1273 at IM 50 mcg (0.25 mL) per dose, non-mRNA Nuvaxovid at IM 5mcg (0.5mL) per dose, Comirnaty Bivalent (Original/Omicron BA.4/5) at IM 30 mcg (0.3 mL) per dose, and Moderna/Spikevax Bivalent (Original/Omicron BA.1) at IM 50 mcg (0.5 mL) per dose. The booster dose is meant as a single dose.

WHO approved Covaxin under the EUL procedure for use in two doses for primary vaccination. The storage condition, dosing, formulation and administration of the vaccines used in this study will be according to the package insert approved by WHO EUL. As Covaxin has not been approved for booster, this study will be investigating Covaxin as a booster dose at single IM 6ug (0.5ml) per dose.

### **8.3. Study Drug Administration**

At the time of writing (02 Nov 2022), five COVID-19 vaccines (the mRNA vaccines BNT162b2 and mRNA-1273, the bivalent Comirnaty (Original/Omicron BA.4/5) and Moderna/Spikevax (Original/Omicron BA.1) vaccines, and the non-mRNA Nuvaxovid) have been authorised by HSA for use in Singapore. The storage condition, dosing, formulation and administration of the vaccines used in this study will be according to prevailing recommendations provided by MOH and the conditions of the PSAR approval. This study is following the MOH's guideline of giving BNT162b2 at IM 30 mcg (0.3 mL) per dose, mRNA-1273 at IM 50 mcg (0.25 mL) per dose, non-mRNA Nuvaxovid at IM 5mcg (0.5mL) per dose, Comirnaty Bivalent (Original/Omicron BA.4/5) at IM 30 mcg (0.3 mL) per dose, and Moderna/Spikevax Bivalent (Original/Omicron BA.1) at IM 50 mcg (0.5 mL) per dose. The booster dose is meant as a single dose.

WHO approved Covaxin under the EUL procedure for use in two doses for primary vaccination. The storage condition, dosing, formulation and administration of the vaccines used in this study will be according to the package insert approved by WHO EUL. As Covaxin has not been approved for booster, this study will be investigating Covaxin as a booster dose at single IM 6ug (0.5ml) per dose.

### **8.4. Specific Restrictions / Requirements**

There will be no restrictions on medications, herbs, vitamins and mineral supplements imposed on study participants.

### **8.5. Blinding**

Only study participants will be blinded to the vaccine allocation. This is to reduce the risk of bias in participant-reported AEs. The study participant will be unblinded at the Day-28 visit (Visit 3) and the vaccination details recorded in the participant's national immunisation record.

### **8.6. Concomitant therapy**

There will be no restrictions on diet, exercise or concomitant medication imposed on participants, except for the restriction of receiving any other COVID-19 vaccines outside of this study.

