Since the first detection of the XBB Omicron subvariant in August 2022 in India, it has been detected in more than 17 countries to-date including Singapore, Australia, Bangladesh, Denmark, Japan and the US. The current wave of COVID-19 cases in Singapore, driven by the XBB strain, is expected to peak in mid-November 2022 with about 15,000 daily cases on average. The proportion of reinfections among total COVID-19 cases in Singapore is also on the rise, currently making up about 17% of total new cases. To combat the rising COVID-19 infections and reinfections, the bivalent Moderna/Spikevax vaccine was added to the National Vaccination Programme from 14 October 2022 for persons who have yet to achieve minimum protection (i.e. received at least 3 doses of mRNA/Nuvaxovid or 4 doses of Sinovac-Coronavac), or those aged 50 years and above who have received their last vaccine dose more than five months ago. On 25 October 2022, Singapore's HSA granted interim authorisation of a booster dose of the Pfizer-BioNTech bivalent vaccine for individuals aged 12 years and older.

From 14 Nov 2022, a second booster dose from five months to one year after the last vaccine dose is recommended by MOH for all individuals aged 18 years or older.

The updated bivalent vaccine is preferred for this. A person is considered up-to-date with their COVID-19 vaccination if they have received at least the minimum protection and their last vaccine dose was received within the past one year. The bivalent Moderna/Spikevax vaccine is currently available, and the bivalent Pfizer-BioNTech vaccine is expected to be available by the end of this year.

PRIBIVAC will assess a heterologous prime-boost-boost strategy in comparison with a homologous regimen in order to compare short and long-term immunogenicity of different COVID-19 vaccine combinations against the ancestral SARS-CoV-2 as well as different VOCs. Initial phases of the study have studied homologous versus heterologous vaccines at the first booster, later phases will study these as the second booster.

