#### **d. Rationale for Study Design**

PRIBIVAC is an adaptive, randomised, subject-blinded, controlled trial to assess the immunogenicity and safety of heterologous boost COVID-19 vaccine regimens compared with a homologous boost regimen. Potential participants would have already received a primary vaccine series with BNT162b2 or mRNA-1273 prior to randomisation.

In Phases A-C of this study, the booster vaccine for the control group was the homologous mRNA vaccine (e.g. BNT162b2 + BNT162b2 or mRNA-1273 + mRNA-1273), while the heterologous vaccine candidates were an alternative COVID-19 vaccine. For individuals randomised to intervention group 1 the mRNA booster vaccine administered was heterologous to the primary series (e.g. BNT162b2 + mRNA-1273 or mRNA-1273 + BNT162b2), while for other intervention groups this included vaccines of alternate designs:

- Control group: Homologous mRNA booster vaccine
- Intervention group 1: Heterologous mRNA booster vaccine (Phase A)
- Intervention group 2: COVAXIN® (Phase B)
- Intervention group 3: Nuvaxovid (Phase C)

Vaccine candidates in phases A-C entered the study at different time points and participants were randomised at equal probability to the available intervention arms at the time of randomisation. This will reduce the risk of bias (e.g. participant preference for a certain arm) compared with a non-randomised design. While an ideal scenario is to have all the selected vaccines approved prior to the start of recruitment, due to the unknown time of availability of vaccine candidates A, B and C, and the urgency of the current situation, recruitment to the control and intervention group 1 (Phase A) was initiated from 12 Oct 2021. Intervention group 2 (Phase B) was added in January 2022 and discontinued 15 March 2022 per the recommendation from the Data Safety Monitoring Board, who reviewed the trial's preliminary results from the first 10 COVAXIN recipients up to Day 28 post-booster. Recruitment to Intervention group 3 (Phase C) was terminated prior to initiation due to delays in the availability of Nuvaxovid which despite receiving interim authorisation by HSA in February 2022 has only become available for administration in late May 2022.

As of 18-May-2022 uptake of the first booster has increased to 75% of the population – with a sharp increase in uptake from January 2022 following governmental policy changes to the definitions of vaccinated status. A significant proportion of those who have not taken their

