### 3.5. Withdrawal Criteria

The participant may be withdrawn prematurely from the trial if he/she withdraws consent to participate in the study. In such instances, the withdrawal will be applicable to both data collection as well as vaccination.

Participants may voluntarily decline the booster vaccination, or they may be withdrawn by their attending physician and/or by the study investigator(s) on the basis of the participant's best interest. Even if the participant did not receive the booster vaccination, collected samples will still be analysed up until the point the participant withdraws consent.

All participants, including those who declined the booster vaccination, will be followed up until 12 months, unless the subject withdraws informed consent or is lost to follow-up or have died.

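### Section 8.6 bars outside COVID-19 vaccines with no exception for recipients in the stopped COVAXIN arm, who come under a national dose offer before their follow-up ends

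*Protocol*

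**What the plan says.** Protocol Section 8.6 sets one limit on what participants may take: no restrictions "except for the restriction of receiving any other COVID-19 vaccines outside of this study". It gives no end date and no exception by arm.

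Section 1.2 d records that the COVAXIN arm was added in January 2022 and "discontinued 15 March 2022 per the recommendation from the Data Safety Monitoring Board", after a review of the first 10 recipients up to Day 28. It does not give the ground. Section 9.4 allows the board to recommend stopping an arm for safety, for futility in immunogenicity, or for both.

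Section 1.2 a describes two national offers. From 14 October 2022 the bivalent vaccine is in the national programme for people below minimum protection, defined as having "received at least 3 doses of mRNA/Nuvaxovid or 4 doses of Sinovac-Coronavac", and for those aged 50 or over whose last dose was more than five months ago. From 14 November 2022, "a second booster dose from five months to one year after the last vaccine dose is recommended by MOH for all individuals" aged 18 or older. COVAXIN is not named in the first definition. Section 5.1 calls Nuvaxovid the first non-mRNA vaccine accepted as a booster in Singapore and notes that a COVAXIN booster is not approved under the WHO listing.

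The only further dose inside the study is Phase D. Section 3.3 requires a first booster of BNT162b2 or mRNA-1273 for entry, and Section 3.4 lifts exclusions 1 and 4 only.

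**The concern.** A bar on outside vaccines is sensible while an arm is producing durability data. The COVAXIN recipients are in a different position. Their arm has been stopped, their booster is not on the protocol's own list of doses that count, Phase D is closed to them, and they were unblinded at Day 28 (Section 8.5), so they know which vaccine they had. The protocol describes a national dose offer that covers them and, in 8.6, forbids them to take it outside the study. At stake is later protection for at least 10 people during the XBB wave that Section 1.2 a describes.

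**Working it through.** No sample size, power or error rate is involved, so there is no stated figure to reproduce. The check compares sections and counts days.

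**Are these recipients covered by an offer?**
- If COVAXIN does not count towards minimum protection, two mRNA doses plus COVAXIN leave two qualifying doses against the three required. The bivalent programme covers them from 14 October 2022.
- If COVAXIN counts, five months (152 days) after a dose given between 1 January and 15 March 2022 falls between 2 June and 14 August 2022. All are therefore past five months by 14 November 2022 and inside that recommendation. Those aged 50 or over would also be past five months by 14 October; their number is not given.

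On either reading an offer applies before follow-up ends.

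**How long does the bar remain?** Inputs and assumptions:
- The end of the bar is assumed to be Day 360, because 8.6 gives no end and Section 3.5 follows participants for 12 months.
- The earliest dose is assumed to be 1 January 2022, because Section 1.2 d gives only the month.
- The latest dose is assumed to be 15 March 2022, the date the arm stopped.
- The 10 reviewed recipients were dosed by about 22 February 2022 (15 March minus 21 days, since the Day 28 visit may fall 7 days early).
- As a sensitivity case, someone randomised on 15 March could be dosed 28 days later, on 12 April, because screening may precede vaccination by up to 28 days.

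Days remaining = (dose date + 360 days) − date of the offer.

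| Dose date | Day 360 | Days from 14 Oct 2022 | Days from 14 Nov 2022 |
|---|---|---|---|
| 1 Jan 2022 | 27 Dec 2022 | 74 | 43 |
| 22 Feb 2022 | 17 Feb 2023 | 126 | 95 |
| 15 Mar 2022 | 10 Mar 2023 | 147 | 116 |
| 12 Apr 2022 (sensitivity) | 7 Apr 2023 | 175 | 144 |

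The 14-day visit window either side widens the 1 January to 15 March ranges to 60 to 161 days and 29 to 130 days.

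**Late or missed?** The November recommendation runs to one year after the last dose. Day 360 is 5 days inside 365, so a dose taken straight after an on-time final visit still meets it. A visit at Day 374 would be 9 days past. The text on minimum protection states no such limit.

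**What would a release now put at risk?** The Day 180 window closes at Day 194. That is 25 September 2022 for a dose on 15 March, and 23 October 2022 for a dose on 12 April. Both precede 02 November 2022, the time of writing given in Section 7.1. Only Day 360 samples and the last months of infection and safety data remain exposed.

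**How much delay could an amendment recover?** Section 12.1 requires ethics approval. Its duration is not given. Assuming 4 to 8 weeks from 14 November:
- 4 weeks: 43 − 28 = 15 days to 116 − 28 = 88 days
- 8 weeks: 43 − 56 is below zero, so 0 days, to 116 − 56 = 60 days

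**The case against.** The strongest case against is that a uniform bar is ordinary practice in an immunogenicity trial. Releasing one arm puts an arm-specific outside dose before Day 360, while Section 11.2 a keeps stopped arms in the analysis. With 10 documented recipients, flagging or censoring could remove much of that arm's Day 360 data. This is the true price of the change. It falls on late secondary and exploratory data in an arm already stopped.

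The October limb rests on COVAXIN being absent from a short background account of national policy; whether MOH counted it is not shown. The November limb does not depend on that. The consent form and the monitoring board's charter are also not shown and might contain a release. Section 12.1's duty to pass on new information is a duty to inform and gives no permission to take a dose.

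Three stronger readings are tempting, and the documents do not support them:
- **A recipient must wait or withdraw and be lost.** Section 6.3 d says "Participants are free to withdraw from the study at any time without any consequence", and Section 3.5 says that on withdrawal of consent "the withdrawal will be applicable to both data collection as well as vaccination". But Section 3.5 ends follow-up only on withdrawn consent, loss to follow-up or death. Someone who takes an outside dose breaches 8.6 and stays in follow-up.
- **The bar also binds those who decline the study dose.** Section 3.5 says "All participants, including those who declined the booster vaccination, will be followed up until 12 months", which invites this reading. But the phrase about any other vaccine most naturally presupposes a study dose. The number of such people is unknown and may be zero, and they are in neither analysis set of Section 11.2 a.
- **The bar harms the trial generally.** Nothing here bears on the Day 28 primary endpoint or on vaccinated mRNA and Phase D participants, whose durability data the bar properly protects.

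**Conclusion.** The point holds in a narrow form: 8.6 gives COVAXIN recipients no permission to take a nationally offered dose during follow-up, and the study offers them no other. The delay is 74 to 147 days from 14 October 2022, or 43 to 116 days from 14 November 2022, less the time that approval of an amendment would take. These figures rest on the bar ending at Day 360 and on doses between 1 January and 15 March 2022. The October figure also rests on COVAXIN not counting towards minimum protection. Under the November recommendation alone the dose is delayed, provided the final visit is not late. The number affected is small (10 documented, full arm size not given). This is an improvement worth considering, with medium confidence, and no threat to the trial's conclusions.

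**What to change.** Add to Section 8.6 that COVAXIN recipients, once past Day 28, may take any COVID-19 dose MOH recommends to them and remain in follow-up. Tell the current recipients. Record the date and brand of any such dose, and flag or censor that participant's later immunogenicity, infection and SAE data from that date.

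The cost is a sentence or two in the protocol, matching consent wording, ethics approval (which uses up some of the remaining time), a notice to at least 10 people and a field for date and brand on the case report form. The scientific price is that some Day 360 antibody, T-cell and mucosal samples, and some late infection and safety data in this arm, will follow an outside dose. The Day 28 endpoint and this arm's Day 180 samples are untouched.

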## **9. SAFETY MEASUREMENTS**

### **9.1. Definitions**

Safety will be assessed using the FDA Guidance Document (2007): Toxicity Grading Scale for Healthy Adult and Adolescent Volunteers Enrolled in Preventive Vaccine Clinical Trial (<http://www.fda.gov/BiologicsBloodVaccines/GuidanceComplianceRegulatoryInformation/Guidances/Vaccines/ucm074786.htm>). Participants will be monitored up to Visit 2 (Day 7) for the occurrence and nature of any AEs.

All AEs will be entered in the appropriate e-CRF (including seriousness, grade, severity, relationship to the IP and action taken) and in the source documents. The hospital laboratory will perform investigational tests as specified in the trial schedule, including full blood count (with differential blood count and platelet count), liver panel (total bilirubin, ALP, ALT), renal panel (sodium, potassium and creatinine), creatine kinase, troponin, and pregnancy test if indicated.

For out-of-range values, clinical laboratory reports must be reviewed by a physician within 24 hours of receipt. Out-of-range values will be evaluated as either clinically significant (CS) or not clinically significant (NS). By definition, a value flagged as “CS” must be entered on the AE page in the CRF. The test may be repeated at the Investigator’s discretion. The Investigator may use his own judgment to determine whether the abnormal finding has sufficient reasons to immediately withdraw the participant from the study.

Any laboratory value that meets the definition of a SAE (see Section 9.3.) must be reported.

### **9.2. Collecting, Recording and Reporting of “Unanticipated Problems Involving Risk to Subjects or Others” – UPIRTSO events to the NHG Domain Specific Review Boards (DSRB)**

**UPIRTSO events** refers to problems, in general, to include any incident, experience, or outcome (including AEs) that meets ALL of the following criteria:

#### **1. Unexpected**

In terms of nature, severity or frequency of the problem as described in the study documentation (eg: Protocol, Consent documents etc).

#### **2. Related or possibly related to participation in the research**

Possibly related means there is a reasonable possibility that the problem may have been caused by the procedures involved in the research; and

#### **3. Risk of harm**

Suggests that the research places participants or others at a greater risk of harm (including physical, psychological, economic, or social harm) than was previously known or recognized.

#### **Reporting Timeline for UPIRTSO Events to the NHG DSRB.**

- 1. Urgent Reporting:** All problems involving local deaths, whether related or not, should be reported immediately – within 24 hours after first knowledge by the NHG investigator.

2. Expedited Reporting: All other problems must be reported as soon as possible but not later than 7 calendar days after first knowledge by the NHG investigator.

